**Secondary outcomes**

Differences in other plasma proteins or metabolic products, based on the completion of the primary outcome measures.

## Statistical methods

The Shapiro–Wilk test will be performed to determine normality for continuous variables. Descriptive statistics will be presented as mean ± SD for normally distributed continuous variables while those with a non-normal distribution as median interquartile range (IQR)..

In this study, proteomic data will be processed using Spectronaut Pulsar, with raw data files converted to a standard format by local normalization. The data will undergo pre-processing to remove low-quality spectra and to normalize signal intensities across samples. Peptide identification will be performed using the UniProt with a false discovery rate (FDR) of 0.01 to control for type I errors. Quantitative data analysis will be conducted using R, where peptide intensities will be compared across samples using *t*-test. Differential expression analysis will be performed to identify significantly regulated proteins, with a *P*-value < 0.05 and foldchange threshold of 1.2 considered statistically significant. Venn analysis will be applied to visualize shared and unique proteins between MICT and HIIT.

When comparing two group means, *t*-test will be used in an unpaired two-tailed fashion. For more than two groups, ANOVA with Bonferroni multiple comparisons test will be used. Adjusted Pearson correlation analysis will be used to assess the association between two factors. All analyses were performed using R (version 4.2.0) software. Statistical significance was set at *P*<0.05 (two-sided).

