Previous research on the mechanisms of exercise has largely centered on understanding how exercise affects specific molecules or pathways, constrained by the available research methodologies. Prior findings have demonstrated that exercise can positively influence mitochondrial quality control in both skeletal and cardiac muscles of mice. This is achieved through the activation of AMPK, which leads to improvements in insulin resistance and an enhancement in stress resistance. [8-12]. Recently, the development of multi-omics technologies and bioinformatics has provided methods to explore comprehensive exercise responses. Using these methods, researchers like Contrepois [13] and Whitham [14] have reported the acute molecular responses of healthy adults to a single session of moderate-intensity exercise. In their studies, during a single session of moderate-intensity exercise thousands of molecular changes and biological processes were revealed, including energy metabolism, oxidative stress, inflammatory responses, tissue repair, growth factor responses, and regulatory pathways. The comprehensive proteomic characteristics between different exercise intensities are not yet clear and have not been reported.

This study intends to use a crossover trial design, employing non-specific proteomics techniques and bioinformatics methods to map the molecular responses of adult plasma to MICT and HIIT. This research will be the first to explore proteins specifically and co-expressed in both forms of exercise, providing data support and direction for subsequent research in precise exercise therapy; it will also provide information for the development of exercise mimetics, allowing patients who are unable to participate in exercise due to functional impairments to also gain the health benefits associated with exercise.

**We hypothesize** that the HIIT will induce a distinctive plasma protein response in contrast to MICT.

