## Outcomes

**Primary outcome**

Any differentially expressed plasma proteins or metabolic molecules observed after HIIT and MICT.

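### Mode-specific proteins are sorted by a Venn diagram, and no within-person test of HIIT change against MICT change is specified

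*Protocol*

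**What the plan says.** Section 3.1 (Rationale) hypothesises that "the HIIT will induce a distinctive plasma protein response in contrast to MICT", and describes the study as "the first to explore proteins specifically and co-expressed in both forms of exercise". Both statements concern a comparison between modes. The primary outcome (Outcomes) is "Any differentially expressed plasma proteins or metabolic molecules observed after HIIT and MICT", with no contrast defined.

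Statistical methods (section 4.7) gives three relevant elements:

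- A t-test, where "peptide intensities will be compared across samples using" it. The samples to be contrasted are not named. A later sentence makes comparisons of two group means unpaired and two-sided.
- A rule for calling a protein regulated: P below 0.05 together with a "foldchange threshold of 1.2 considered statistically significant".
- The sorting step: "Venn analysis will be applied to visualize shared and unique proteins between MICT and HIIT". This is the only analysis sentence that names both modes. It does not say which lists feed the diagram.

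Table 1, Table 2 and Blood collection give four samples per participant, one before and one after each session. Sample size (section 4.4) plans a 2×2 crossover on a difference between HIIT and MICT.

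**The concern.** A shared-or-unique diagram needs one list per mode, and the sampling supplies one pre-to-post pair per mode. The natural reading is therefore two separate lists, each filtered by the P-value and fold-change rule, and then overlaid.

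Such an overlay compares significance, not response. A protein that passes under HIIT and narrowly fails under MICT is shown as unique to HIIT even if its true change is the same in both. The error also runs the other way: a protein that changes much more under HIIT but passes in both modes is shown as shared.

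The classification is what the study sets out to deliver. The Rationale intends it to guide precise exercise therapy and the development of exercise mimetics, so mislabelled proteins would misdirect later work.

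**Working it through.** **1. The plan's own figure.** The inputs in Sample size are a difference of 21.9, an SD of 15.0, two-sided alpha 0.05 and power 0.80. Taking 15.0 as the within-subject SD and using the normal approximation, N = 2 × [(1.96 + 0.84) × 15.0 / 21.9]² ≈ 7.4, so 8. Allowing for 20% dropout, 8 / 0.80 = 10. Both stated numbers are reproduced. The planned quantity is a between-mode difference, so the 0.80 is not the power to detect a pre-to-post change within one mode. The Protocol does not give that power.

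**2. Overlaying two lists.** Suppose a protein has the same true change in both modes and enters each list independently with probability p. Then:

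- on both lists: p²
- on exactly one list: 2p(1−p)
- share of detected proteins labelled unique: 2p(1−p) / [1 − (1−p)²] = 2(1−p) / (2−p)

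| p (assumed) | Exactly one list | Share of detected labelled unique |
| --- | --- | --- |
| 0.30 | 42% | 82% |
| 0.50 | 50% | 67% |
| 0.80 | 32% | 33% |
| 0.90 | 18% | 18% |
| 0.95 | 9.5% | 10% |

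**3. Simulation with the plan's entry rule.** From the Protocol: 10 men, four samples each, P below 0.05 and fold change above 1.2. Assumed, because the Protocol gives neither: CV 30% and within-person correlation 0.5 to 0.8. The true fold change is equal in both modes, so every unique label is wrong. Ranges run over the two correlations; figures can move by a point or two between runs.

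| True fold change | Unpaired, share of detected | Paired, share of detected | Unpaired, share of all |
| --- | --- | --- | --- |
| 1.2 | 86–87% | 67–77% | 20–31% |
| 1.3 | 57–67% | 17–48% | 38–46% |
| 1.5 | 8–18% | 0–6% | 8–17% |
| 1.75 | under 1% | under 1% | under 1% |

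With 8 men, the evaluable number in Sample size, the unpaired share of detected is 88–90%, 67–75% and 21–33% at fold changes of 1.2, 1.3 and 1.5.

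**4. A second set of assumptions.** With log2 SDs of 0.4 between and 0.3 within participants, and equal true log2 changes of 0.3 to 0.6, the share of detected labelled unique at 10 men is 30–88% unpaired and 5–69% paired. Of the proteins on exactly one list, the direct contrast is non-significant in 84–91%.

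**5. The direct contrast.** Testing (post − pre under HIIT) minus (post − pre under MICT) within each man calls a difference in about 5% of all equal-response proteins, before multiplicity control. The like-for-like comparator is the last column of the table in step 3, not the shares of detected.

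**6. The between-mode test that the text allows.** An unpaired t-test of post-HIIT against post-MICT values treats the same men as two independent groups. With within-person correlation r, it overstates the standard error by a factor of 1/√(1−r): 1.41 at r = 0.5 and 2.24 at r = 0.8. In simulation its false-positive rate is about 0–1% against a nominal 5%, so it is badly conservative. It also makes no use of the pre-exercise samples.

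**The case against.** **The hypothesis is not left untested.** A reader might infer that no test of the hypothesis exists. The Protocol does not support that. Its t-test for two group means can be applied to HIIT against MICT, and the sample size presumes such a comparison. This stands. What remains is that the test is not named for this purpose, is unpaired, and is not linked to the unique label.

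**The two lists are inferred, and the diagram only visualises.** Both points are fair as a reading of the sentence. But no other rule in the Protocol decides which proteins are specific, and that decision is a stated aim.

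**The largest figures come from a chosen scenario.** This stands. A true fold change of 1.2 lies on the plan's own cutoff, so an estimate exceeds it only about half the time. With p at most about 0.5, the share of detected labelled unique cannot fall much below 67% at any sample size; paired tests with 200 men still give 65–68%. A reader might infer that most shared responses will be mislabelled. That holds only near the cutoff; well above it the problem almost vanishes.

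**A separate SAP may add the contrast, and the study is exploratory.** An SAP could do so, and Sample size does call the study exploratory. But the Protocol itself states both the sorting step and the unpaired test, and an SAP that followed it would inherit both. The Rationale also states a hypothesis and downstream uses.

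**Conclusion.** The concern holds in a limited form. Section 4.7 specifies no within-person test of whether the change differs between HIIT and MICT, and the one step that sorts proteins into shared and unique cannot show such a difference.

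The consequence depends on power. It is largest for changes near 1.2-fold, substantial at 1.3, modest at 1.5 and negligible at 1.75. Unpaired testing enlarges it wherever it is not already negligible. As a share of all equal-response proteins with unpaired tests, the wrong label falls on 20–31%, 38–46% and 8–17% at fold changes of 1.2, 1.3 and 1.5, against about 5% for the direct contrast.

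These sizes rest on the inferred reading of two per-mode lists and on an assumed CV of 30% and correlation of 0.5 to 0.8. The argument that list membership does not measure a difference needs none of the numerical assumptions.

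**What to change.** In section 4.7:

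- Decide mode-specificity by the within-person contrast, HIIT change minus MICT change, with period in the model and FDR control across proteins.
- Call a protein HIIT-specific or MICT-specific only if that contrast is significant.
- Report the estimate and 95% CI of the contrast for every protein on either list.
- Keep the Venn diagram as a descriptive figure, name the lists that feed it, and draw no inference from its sectors.

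The cost is revised wording and one further contrast from the four samples already planned per man. The downside is that fewer proteins will be called mode-specific. With equal variances and correlations, the contrast has √2 times the standard error of a single-mode change, and FDR control raises the bar further.

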# METHODS

## Trial design

This is an open-label, randomised crossover trial.

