## Sample size

This study is exploratory in nature, with the primary research indicator being the observation of any difference in plasma proteins or metabolic products after HIIT and MICT. Since there are currently no research reports comparing the proteomic or metabolomic results of HIIT and MICT, this study is based on the team's previously published research on HIIT and MICT improvements in adult fasting blood glucose, estimating a difference of 21.9 units for a certain protein or metabolic product between the two groups, with a standard deviation of 15.0 units (Yaoshan Dun, Randal J. Thomas, Joshua R. Smith et al. High-intensity interval training improves metabolic syndrome and body composition in outpatient cardiac rehabilitation patients with myocardial infarction. Cardiovascular Diabetology. 2019;18:104). With a Type I error α=0.05 and a test power of 1-*β*=0.8, the study design method selected is a 2*2 crossover trial design, with the outcome indicator type as a continuous variable. It was calculated that a total of 8 participants are needed, and considering a 20% dropout rate, 10 participants should ultimately be included. The calculations were completed using PASS 15.0.5 software.

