**Blood collection**

In this study, professional medical personnel will perform 4 venous blood collections for each participant, corresponding to before and after the two exercise interventions. Each blood collection will be 10 ml, collected using non-anticoagulant tubes, left at room temperature for 2 hours, then centrifuged at 2-8℃ at 1000g for 15 minutes, and the supernatant is taken and stored at -20℃ or -80℃ for subsequent testing and analysis.

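### The protocol prescribes an unpaired t-test for comparisons that its crossover design makes within-person; with positive within-person correlation the cost is missed proteins, not extra false positives

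*Protocol*

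**What the plan says.** Trial design states: "This is an open-label, randomised crossover trial". Sample size says that "the study design method selected is a 2*2 crossover trial design, with the outcome indicator type as a continuous variable", and arrives at 8 participants, raised to 10 for 20% dropout. Blood collection provides for "4 venous blood collections for each participant, corresponding to before and after the two exercise interventions", and Table 2 places these samples 5 minutes before and 15 minutes after each session, with a two-week washout between sessions.

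Statistical methods gives three rules for tests:

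- In the differential-expression paragraph, "peptide intensities will be compared across samples using *t*-test". Pairing is not mentioned there.
- For any comparison of two group means, the t-test "will be used in an unpaired two-tailed fashion". This is the only statement on pairing in the protocol, and it is not restricted to any type of comparison.
- "For more than two groups, ANOVA with Bonferroni multiple comparisons test will be used". No participant term or repeated-measures form is named.

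A protein counts as differentially expressed if P<0.05 and the fold change reaches 1.2. A Venn analysis then shows which proteins are shared between the modes and which are unique to one.

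**The concern.** An unpaired t-test assumes that the two sets of values come from different, independent people. Here they come from the same men. Stable differences between men, which cancel in a within-person comparison, go into the error term instead. The crossover was chosen, and the trial sized, to remove exactly that variation.

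The list of differentially expressed proteins is the primary outcome, so a loss of sensitivity falls directly on it. It also affects the Venn display: a protein that responds to both modes but passes the rule in only one is shown as unique to that mode. The lower the power, the larger the share of displayed proteins that this can affect. The trial's hypothesis is that HIIT produces a distinctive response, so the shared-versus-unique split matters to its main message.

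**Working it through.** **1. The protocol's own sample size.** Inputs from Sample size: difference 21.9, SD 15.0, "With a Type I error α=0.05 and a test power of 1-*β*=0.8", 2x2 crossover. Two-sided testing is stated in Statistical methods. Taking 15.0 as the within-subject SD and using the normal approximation:

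N = 2 × (1.960 + 0.842)² × (15.0/21.9)² = 7.36, so 8.

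Allowing for 20% dropout, 8/0.8 = 10. The stated 8 and 10 are reproduced as a crossover calculation. With 15.0 as the SD of paired differences and a noncentral t on N−2 degrees of freedom, power is 0.76 at 6 and 0.93 at 8, so the smallest even N is again 8. With 15.0 as within-subject SD and the same exact method, power is 0.68 at 8 and 0.82 at 10.

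**2. What the unpaired test does to the standard error.** Let σ be the total SD, r the within-person correlation and n the number of men. The mean difference has true variance 2σ²(1−r)/n, but the unpaired test works with 2σ²/n. Its standard error is too large by a factor of about 1/√(1−r): 1.41 at r=0.5 and 2.24 at r=0.8.

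**3. Effect under the protocol's decision rule.** Assumptions, none given in the protocol: log-normal intensities, CV 30% (log-scale SD √ln(1+0.3²) = 0.294), n=10. Each cell is the simulated chance of meeting both P<0.05 and a fold change of at least 1.2.

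| True fold change | r | Unpaired | Paired |
| --- | --- | --- | --- |
| 1.2 | 0 | 26% | 23% |
| 1.2 | 0.3 | 23% | 31% |
| 1.2 | 0.5 | 20% | 38% |
| 1.2 | 0.8 | 14% | 50% |
| 1.5 | 0.3 | 87% | 90% |
| 1.5 | 0.5 | 90% | 97% |

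These are simulated values and can move by about a point between runs; a repeat run gave 24% for the paired test at r=0 and 30% at r=0.3.

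The pattern can be checked by hand. The unpaired test typically needs an estimated log difference of 2.101 × 0.294 × √(2/10) = 0.276, a fold change of about 1.32, so P<0.05 is the binding condition. At r=0.8 the paired test needs 2.262 × 0.294 × √(2/10) × √0.2 = 0.133, a fold change of about 1.14, so the 1.2 rule binds. With a true value of exactly 1.2, about half of the estimates then fall short, which is why the paired figure stops near 50%. On P<0.05 alone it would be 79%.

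**4. True type I error of the unpaired test** (P<0.05 alone, nominal 5%, n=10): about 2.2% at r=0.3, 0.9% at r=0.5 and below 0.1% at r=0.8. The paired test stays at about 5%.

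**5. On the protocol's planning values with 8 completers**, unpaired versus period-adjusted crossover analysis, P<0.05 alone:

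| Meaning of SD 15.0 | r=0.5 | r=0.7 | r=0.8 |
| --- | --- | --- | --- |
| SD of paired differences | 0.84 vs 0.93 | 0.60 vs 0.93 | 0.37 vs 0.93 |
| Within-subject SD | 0.49 vs 0.69 | 0.26 vs 0.68 | 0.12 vs 0.68 |
| Total SD | 0.84 vs 0.93 | 0.87 vs 0.99 | 0.89 vs 1.00 |

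**6. Period.** Suppose there is no mode effect, the response is 0.5 log units lower in the second session, and 5 MICT-first and 3 HIIT-first men complete. The HIIT-minus-MICT difference in change is −0.5 in the first group and +0.5 in the second. The plain paired mean is (5×(−0.5) + 3×0.5)/8 = −0.125. The average of the two sequence means, which is the period-adjusted estimate, is 0. With 5 completers in each sequence the plain mean is also 0.

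**The case against.** **The error is conservative and the study is exploratory.** This stands. A reader might infer from an invalid independence assumption that false positives are inflated. With positive within-person correlation the opposite is true, as step 4 shows. The harm is missed proteins, and P-values that do not mean what they say.

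**The loss may be small.** Also fair. At r=0 the unpaired test is slightly better, because it keeps more error degrees of freedom. At fold change 1.5 the difference is a few points at r=0.3 and r=0.5. If 15.0 is a total SD, the unpaired test still exceeds 80% power at 8 completers in the settings shown. For HIIT versus MICT the relevant r is the one between two change scores, which may be well below that of raw intensities. The 79% at r=0.8 should not be quoted as the paired result, since it ignores the fold-change rule.

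**The statistical analysis plan may settle it.** Period and sequence terms, and the use of the pre-exercise samples as baselines, are commonly left there, so their absence is no fault in itself. The unpaired instruction is different: it is stated positively, and a plan that named a paired test would contradict it.

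**ANOVA.** A reader might infer that ordinary one-way ANOVA is prescribed. The text does not say so; a repeated-measures form is neither named nor ruled out.

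**Period bias.** A reader might infer that ignoring period biases the comparison. Enrolment and randomisation fixes five men per sequence, so the mean contrast is unbiased if all complete. Bias needs unequal dropout.

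**Unpaired tests have a place**, for example in comparing baseline data between the sequence groups. The protocol does not confine them to that.

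**Conclusion.** The point holds in this form: the unpaired rule is wrong for the trial's main comparisons, because it contradicts the crossover design, the sampling scheme and the basis of the sample size. That conclusion needs no assumption about the data.

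The size of the loss does. Under the assumptions in step 3 and a true fold change of 1.2, it runs from no loss at r=0 to a detection chance of 14% instead of 50% at r=0.8. It is small for larger effects or low correlation.

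The documents do not support reading this as inflated false positives, as an error in the planned number of 8 or 10 (which reproduces as a crossover calculation), or as a bias from period effects under complete follow-up.

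**What to change.** Replace the sentence on unpaired t-tests with wording to this effect:

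- For each protein, compute the log2 post-minus-pre change within each session.
- Test the change within each mode with a paired, within-participant test.
- Compare HIIT with MICT by a crossover analysis of the two change scores, with participant, mode and period terms. A mixed model on all four samples is equivalent if it includes period-by-time and allows for session within participant. A period main effect alone is not enough, because it shifts a session's pre and post samples equally and cancels from the change-score contrast; the −0.125 of step 6 would remain. Moderated variances (limma) are optional.
- State that any ANOVA on repeated samples includes a participant term.
- Confine unpaired tests to comparisons between different people, such as baseline by sequence group.

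The cost is wording and a few lines of R. No further samples or participants are needed, and the planned number does not change. Some error degrees of freedom are lost, which matters only if the within-person correlation is near zero.

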## Participant timeline

**Expected duration of the trial**

Duration per participant: 3 months.

**Time plan:** Start: May 2023

First inclusion of participants: May 2023

Inclusion of all participants: Dependent

All participants completed the study: Dependent

## Recruitment

All participants will be recruited from the Hospital.

## Assignment and allocation of intervention

After informed consent and screening, participants will be randomised (1:1) to the MICT-first group and HIIT-first groups.

**Sequence generation:** For allocation of participants, an investigator with no involvement in the intervention part of the trial will prepare a computer-generated list of random numbers that will be used to assign participants in a 1:1 ratio to the MICT-first and HIIT-first groups.

**Concealment mechanism:** The allocation sequence will be concealed from the researcher enrolling and assessing participants in sequentially numbered, opaque, sealed, and stapled envelopes.

**Implementation:** After acceptance of a participant by the panel, and before admission to a group, the appropriate numbered envelope will be opened; the card inside will inform if the participant is to be assigned to the MICT-first or the HIIT-first group, and this information will then be given to the researchers responsible for intervention.

